### MRI protocol and procedures

2.6.

The Aspect Embrace Neonatal MRI System is an FDA-approved device which uses innovative technology to safely and effectively perform infant brain imaging while they remain within the NICU. The BWH NICU houses a 1 Tesla in-unit MRI infant scanner with a built-in incubator, self-contained magnet, and continuous video monitoring.

#### Timeline of MRI scans

2.6.1.

In our NICU, the clinical standard of care entails that babies born extremely preterm (before 28 weeks gestation), or VP (28–32 weeks gestation) with additional risk factors such as moderate-severe bronchopulmonary dysplasia, stage II or higher necrotizing enterocolitis, need for major surgery, severe growth restriction, or documented neurological abnormality on CUS among others, are considered for a TEA brain MRI. The TEA scan typically occurs between 38 and 42 weeks PMA or within the week of discharge, whichever comes first. Infants typically undergo brain MRI scanning without sedation in the study unit (20), using the documented “feed and wrap” method (32) (Figure 2). Serial CUS imaging is also obtained routinely in our unit for babies born before 32 weeks gestation per a clinical practice guideline, typically on days of life 1, 3, 7, 30, and 60. However, with only scarce evidence-based understanding of the etiology of many neuronal disorders available, findings on both serial CUS and TEA MRIs leave many unanswered questions in terms of etiology, timing, and evolution of injury prior to TEA, which have implications for the child's developmental trajectory and therapy needs post NICU discharge.

**Figure 2 F2:**
[figure not shown]
Procedure for brain MRI: infant wrapped in MRI-safe jacket is placed in Embrace Aspect scanner.

For both the low-risk and high-risk groups, we aim to obtain a first, early MRI once the infant is enrolled by 32 weeks PMA, and as soon as clinical status permits. Importantly, infants will need to be off mechanical ventilation and stable on continuous positive airway pressure as the maximal level of respiratory support to be able to undergo an in-unit MRI. This initial MRI will be used to understand the nature of any brain injury with systematic criteria for low or high neurodevelopmental risk as outlined above (i.e., enrolled VP infants with IVH with any ventricular dilation, moderate or severe WMI, and/or cerebellar hemorrhage will be assigned to the high-risk group; enrolled VP infants not meeting this criteria will be assigned to the low-risk group).

An infant will subsequently be assigned to the appropriate SENSE risk group (low-risk vs. high-risk) based on the results of the early CUS and MRI findings (if the first brain MRI is able to be completed at enrollment). If an infant is in a critical condition (i.e., receiving invasive mechanical ventilation or unstable on high level of noninvasive ventilation support) that does not permit safe scanning in the in-unit scanner, we will utilize the CUS results to determine assignment to an SENSE risk group, with plan for the first MRI imaging to be obtained as soon as the clinical status permits. If at any point an infant initially assigned to the low-risk group meets criteria for the high-risk classification based on identification of neurological injury on subsequent imaging, the infant will be transitioned to the SENSE-plus group to received enhanced neurorehabilitative support as outlined in Table 1. Enrolled VP infants in the low- or high-risk groups will be scanned at a frequency of approximately every 2 weeks, from the time of enrollment until TEA (approximately 38–42 weeks PMA) or until NICU discharge, to monitor brain growth and evolution of any injury. At TEA, infants enrolled in the low-risk or high-risk groups will undergo brain MRI in an off-unit Siemens Trio 3 Tesla scanner (Erlangen, Germany) equipped with a 16 channel pediatric head coil and 1 mm isotropic voxels. This schedule of serial imaging will inform characterization of patterns of brain growth of the VP infant throughout their NICU course, along with a broader understanding of the brain injury that occurs over the course of VP infants’ hospitalization.

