### Study subjects

2.3.

The investigation team will recruit consecutive admissions of a total of 75 infants over the course of 2 years. Inclusion criteria consists of: VP infants born at or before 32 weeks of completed gestation based on the best obstetric estimate (or Ballard exam by clinical team if not available), with a birth weight between 0.5–4.5 kg, and deemed to be in stable condition per their clinical team. Families of all races or ethnicities will be included, with study materials available in English and Spanish. Infants will be excluded if they have a confirmed or suspected major congenital anomaly, a genetic syndrome, or congenital TORCH (Toxoplasmosis, Other Agents, Rubella, Cytomegalovirus, and Herpes Simplex) infection.

Study infants in the SENSE program (i.e., exposed group) will be included in one of two groups based on the level of neurological risk documented on early imaging (CUS or MRI):
1)Low-Risk group (*n* = 25) consisting of VP infants *without* significant neurological injury (defined as intraventricular hemorrhage (IVH) with any ventricular dilation, white matter injury (WMI) moderate or severe, cerebellar hemorrhage).2)High-Risk group (*n* = 25) consisting of VP infants *with* significant neurological injury.The reference (i.e., unexposed) group consists of *n* = 25 VP infants who receive the NICU standard of care who are eligible for approach, but do not consent to enrolling in the SENSE program and serial imaging portion of the study. These families will be reapproached for consent for a standard review medical records if their infant undergoes a brain MRI around TEA for an indication unrelated to the current study.

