### Data analysis

2.10.

Descriptive statistics of key demographic and clinical characteristics will be reported overall and by group status (exposed vs. reference) using means and standard deviations (or medians and interquartile ranges, as appropriate) for continuous and number and percentage for categorical variables. Differences by group status will be tested using chi square (or Fisher's exact test where cells <5) and Wilcoxon rank sum or Kruskal-Wallis tests, as appropriate, for categorical and continuous variables, respectively. Similar statistics will be reported by risk status among exposed infants including fidelity of implementation of the SENSE or SENSE-plus program in the low-risk and high-risk groups (>75%, 50%–75%, 25%–50%, and <25% compliance with total amount of recommended sensory exposure in each category). For the primary aim, outcome among infants in the SENSE program (exposed group) will be compared with the unexposed, similarly eligible infants whose families did not enroll in the neuropromotive program. Differences in outcome by group status will be analyzed using linear mixed models [or multinominal regression using generalized estimating equations (GEE) for ordinal categories of injury] to adjust for intrafamilial correlation among multiple births in models unadjusted and adjusted for potential bias (selection and confounding) by baseline covariates associated with both SENSE status and outcome. The study will also examine the difference between groups by exposure and high/low risk status, i.e., high risk: exposed vs. unexposed and low risk: exposed vs. unexposed. To address small sample size, we will utilize robust estimation methods. We will use a similar approach to assess differences between exposure groups for Aim 3 outcomes assessed at NICU discharge and at age two corrected age. Analysis of the change in repeated measures (Aim 2, SENSE groups only) will be modeled using linear mixed models and GEE, as appropriate, with fixed effects for SENSE group status, time, and the interaction between group and time. For assessment of change between two assessment time points, models will include fixed effects for group status and baseline assessment. We will use a similar approach to model Premie-Neuro exam scores (Aim 3) assessed at each serial MRI measurement for exposed infants. Analyses are exploratory and thus multiple comparisons will not be adjusted. Statistical analyses will be run using SAS v9.4 software (SAS Institute Inc., Cary, NC, USA) and IBM SPSS version 24.0 (IBM Corp, Armonk, New York, USA).

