
## Discussion

3.

To our knowledge, this is the first study to follow brain growth and injury in VP infants with serial MRI, and concurrently employ an evidence-based, tailored neuropromotive program before term age with the goal to optimize neurodevelopmental outcomes of VP infants. In this study, our aims are to investigate brain growth and development among VP infants receiving tailored neuropromotive support in the NICU compared to VP reference infants, and to characterize the timing and factors associated with total and regional brain growth and injury on serial brain MRI. Based on the results of initial imaging (initial brain MRI, or CUS if infant clinical status does not permit MRI imaging at the time of enrollment), infants will be assigned to either a low-risk or high-risk group, and subsequently receive protocolized, intensive in-NICU neuropromotive support tailored to their level of neurological risk until TEA. If subsequent imaging of an infant initially in the low-risk group indicates qualification for the high-risk group, the group assignment and the intensity of infant's neurodevelopmental support will be adjusted accordingly. The neuropromotive plan was designed based on an evidence-based program (28), adapted to include additional neurorehabilitative PT/OT support for high-risk infants with established neurological injury. We will explore the associations between risk-stratified NICU neuropromotive programming, and short-term (brain growth, neurobehavior, parent experience) and long-term (child development, family experience) outcomes of VP infants and their families.

The strengths of this study include the capability to obtain serial, in-unit MRI imaging, along with an expert-designed neuropromotive program that has been shown to impact clinical outcomes of VP infants in the NICU. Further, the program intensity will be amplified when higher grade neurological injury is identified, allowing for real-time intensive developmental therapy to facilitate neurorehabilitation. While some associations have been established between early interventions and neurodevelopmental outcomes, this study will contribute important mechanistic data which will broaden our understanding of how neuropromotive interventions can be best tailored for VP infants during a critical window of brain growth and development before TEA, for optimal downstream impact on child and family outcomes.

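### Risk group is updated from later scans in exposed infants only, so if the updated label is used the comparison with reference infants in the low-risk stratum tilts towards SENSE

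*Protocol article*

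**What the plan says.** **Exposed infants.** Section 2.3 places SENSE infants in a risk group; they are "included in one of two groups based on the level of neurological risk documented on early imaging (CUS or MRI"). Section 2.6.1 makes the label one-way changeable. The rule starts "If at any point an infant initially assigned to the low-risk group meets criteria for the high-risk classification based on identification of neurological injury" seen at a later scan, in which case "the infant will be transitioned to the SENSE-plus group". The Discussion (section 3) makes clear that more than therapy changes: "the group assignment and the intensity of infant's neurodevelopmental support will be adjusted accordingly". These infants have an MRI about every 2 weeks until term-equivalent age (TEA) or discharge.

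**Reference infants.** Under sections 2.2 and 2.3 they enter through a TEA MRI done for a reason outside this study. They have no early or serial study MRI, and the article gives no rule for their risk status. They do have routine ultrasound: "Serial CUS imaging is also obtained routinely in our unit for babies born before 32 weeks gestation per a clinical practice guideline", typically on days 1, 3, 7, 30 and 60 (section 2.6.1).

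**Analysis (section 2.10).** Group differences are also to be examined by exposure and risk status, "i.e., high risk: exposed vs. unexposed and low risk: exposed vs. unexposed". The Aim 2 model of repeated measures, restricted to SENSE infants, is specified "with fixed effects for SENSE group status, time, and the interaction between group and time". The text does not say whether group status means status at enrollment or after transition.

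**The concern.** The within-risk comparison needs a stratifier that means the same thing in both arms. Here the only stated label is revised from fortnightly MRI in one arm, while the other arm can be classified only from CUS or from the TEA scan that also supplies the outcome. White matter injury and cerebellar hemorrhage would then be looked for far more often in exposed infants. Late-found cases leave the exposed low-risk stratum, while similar infants stay in the reference low-risk stratum. The exposed stratum looks healthier with no program effect. At stake is the analysis that readers would consult to see whether support tailored to risk works.

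Aim 2 raises a separate question. With the updated label, an infant who transitions has earlier scans, taken on SENSE, counted as SENSE-plus, and group membership is decided by later scans of the series being modelled.

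**Working it through.** **1. The plan's own figures.** Section 2.8 states at least 80% power for d = 0.70, SENSE combined (50) against reference (25), two-sided α = 0.05. The noncentrality is 0.70 × √(50 × 25 / 75) = 2.858 on 73 df, giving power 0.805. The repeated-measures figures also reproduce: 0.41 × √50 = 2.899 gives 0.811, and 0.59 × √25 = 2.95 gives 0.808. The first contrast pools the two risk groups, so the label does not enter it.

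**2. Information available for classification.**

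| Source | Exposed | Reference |
|---|---|---|
| Routine CUS | yes | yes |
| Early MRI | yes, when clinically possible | no |
| Serial MRI | about every 2 weeks | no |
| TEA MRI | study scan | scan for another reason |
| Stated risk rule | early CUS or MRI, then updated | none |

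**3. Low-risk stratum, no SENSE effect.** Let L be the share of early-negative infants whose injury is found later, and δ the injury effect on TEA volume in SD units. Both are assumed. After updating, the exposed low-risk stratum holds uninjured infants only (mean 0). The reference low-risk stratum, classified on early status, has mean L × δ. The spurious difference is therefore −L × δ:

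| L | δ = −0.5 | δ = −1.0 |
|---|---|---|
| 5% | 0.025 | 0.05 |
| 10% | 0.05 | 0.10 |
| 20% | 0.10 | 0.20 |
| 30% | 0.15 | 0.30 |

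A simulation with 30% early injury (also assumed) agrees, running from 0.029 to 0.298. With the same rule and the same detection in both arms, the difference is within 0.005 SD of zero.

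**4. Variant: reference infants classified by CUS alone, exposed infants correctly classified.** Assume 40% injured and CUS sensitivity s. The injured share left in the reference low-risk stratum is 0.4(1 − s) / [0.6 + 0.4(1 − s)]. For s = 0.8 this is 0.08 / 0.68 = 0.118; for s = 0.4 it is 0.24 / 0.84 = 0.286. Multiplied by 0.5 to 1.0 SD, the tilt is about 0.06 to 0.29 SD, much as in step 3.

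**5. High-risk stratum.** If late-found and early-found injuries have equal effects, the difference is zero. It appears only if late-found injuries are milder. For illustration, take 30% early injury at −1.0 SD and 16% late detection at −0.5 SD. Late cases make up 0.70 × 0.16 = 0.112 of infants, or 0.112 / 0.412 = 0.272 of the exposed high-risk stratum, and the tilt is 0.272 × 0.5 = 0.14 SD. Nothing in the article supports the milder-injury assumption.

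**6. Aim 2, no SENSE-plus effect.** Suppose injury lowers growth by δ. The high-minus-low difference is δ(1 − L) with the enrollment label and δ with the updated label. For δ = −0.5 SD, the enrollment label gives −0.45 (L = 10%) or −0.35 (L = 30%), and the updated label gives −0.50. The choice of label changes the estimate; under either label it reflects injury, not the program.

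**The case against.** A reader might infer that both analyses are shown to be biased because reference infants lack an equivalent label. The documents do not support that. The Aim 2 model contains no reference infants, so a missing reference label cannot affect it. Its problem depends on using the updated label, which the Discussion suggests but section 2.10 does not fix. That choice may sit in an analysis plan that is not shown. The transition trigger is also an injury finding and not a tissue volume, and Aim 2 seeks factors associated with growth, so a difference between injured and uninjured infants is not in itself false.

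A reader might also infer that SENSE would look better in both strata, or that reference infants cannot be classified. The first needs late-found injuries to be milder, which is undocumented. The second overlooks routine CUS, which section 2.6.1 already accepts for classifying exposed infants too ill for the scanner.

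These objections narrow the point but do not remove it. The article itself states both the updating rule and the stratified contrast, and defines the stratifier in one arm only. Classifying reference infants from the TEA MRI would narrow the detection gap, but would stratify on the scan that supplies the outcome. Declaring the analyses exploratory covers imprecision and multiplicity; it does not cover a tilt whose direction is known.

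**Conclusion.** The point holds for the within-risk comparison if the updated label is used. Unequal searching for injury then favours SENSE in the low-risk stratum by roughly 0.03 to 0.30 SD under no true effect. This range rests on assumed late detection of 5–30% and an assumed injury effect of −0.5 to −1.0 SD, so the direction is firmer than the size. No tilt in the high-risk stratum is established. For Aim 2 the finding is conditional: the updated label misattributes pre-transition scans and defines group by later scans, and the enrollment label does neither. It would be wrong to extend the point to the primary contrast, which pools low and high risk (section 2.8). The affected analyses are secondary and declared exploratory, but correcting them is cheap and worth doing.

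**What to change.** Leave the clinical transition rule as it is and change only the analysis.

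1. For every exposed-versus-unexposed comparison by risk, use one frozen baseline risk variable for all 75 infants. Derive it from routine CUS, with the same criteria and the same fixed early window in both arms. A fixed day of life suits better than a fixed postmenstrual age: at 32 weeks postmenstrual age an infant born at 26 weeks is 42 days old and has passed the day-30 scan, while one born at 31 weeks is 7 days old. Put infants without routine CUS in a separate category, since eligibility includes 32 weeks but routine CUS is described for births before 32 weeks. Do not use the TEA scan or serial MRI to define these strata.
2. In Aim 2, state that the group effect is risk group at enrollment. Record the transition date and treat transition as a sensitivity analysis, because converters will be few and the term mixes new injury with SENSE-plus.
3. Use MRI-updated risk only descriptively, within the SENSE groups.

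The cost is a few sentences in section 2.10 and one recorded date. CUS misses some MRI-visible injury, so the strata will be less pure, but equally so in both arms.

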### Data collection and management

2.5.

We will utilize the institution's Research Electronic Data Capture (REDCap), a secure, HIPAA compliant application, or a secure Mass General Brigham electronic research drive, for storage of all study data. Parental questionnaires will be directly administered and stored within the REDCap database. Brain MRI files will be transferred directly from the 1 Tesla or 3 Tesla scanner to a research secure server.

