#### MRIs

2.7.1.

As above, we will aim for infants to undergo imaging every 2 weeks with at least 3 serial brain MRIs during the NICU phase: one at the time of enrollment in the study, and as soon as clinical condition allows; one or more interim scans at a frequency of approximately every 2 weeks; and a final scan at TEA in a 3 Tesla, off-unit scanner. We will use an automated segmentation technique (MANTiS) (33) to monitor the primary outcome i.e., evolution of total brain volumetrics as well as tissue-specific volumes of cortical grey matter, deep grey matter, white matter, hippocampus and cerebellum on sequential MRI scans of VP infants in the SENSE and reference groups. Secondary MRI outcomes will include fractional anisotropy in specific brain regions of interest which will be defined based on a validated method (34), and anticipated to include measures of white matter microstructure.

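### The term-equivalent MRI is on a 3T scanner for SENSE infants but on no fixed scanner for reference infants, so scanner may be partly or wholly confounded with exposure in the primary comparison

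*Protocol article*

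**What the plan says.** Section 2.6.1 of the protocol article fixes the final scan of the exposed infants: "At TEA, infants enrolled in the low-risk or high-risk groups will undergo brain MRI in an off-unit Siemens Trio 3 Tesla scanner". Section 2.7.1 repeats it as "a final scan at TEA in a 3 Tesla, off-unit scanner". Their earlier serial scans are done in the unit (section 2.6.1), and section 2.6 states that "The BWH NICU houses a 1 Tesla in-unit MRI infant scanner".

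Reference infants have no study scan. Sections 2.1, 2.2 and 2.3 take their TEA MRI from imaging done for clinical reasons or for other research, and name no scanner or sequence. The nearest description is in section 2.6.1, which sets out the unit's clinical TEA imaging and then says: "Infants typically undergo brain MRI scanning without sedation in the study unit". It refers there to Figure 2, whose caption names the in-unit scanner. Section 2.5 confirms that both field strengths enter the data set, with files "transferred directly from the 1 Tesla or 3 Tesla scanner" to a research server.

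The primary comparison is total brain volume at TEA, SENSE groups combined versus reference (section 2.8), measured by automated segmentation; FA is a secondary MRI outcome (section 2.7.1). Section 2.10 adjusts the primary model for baseline covariates related to both exposure and outcome. It specifies the Aim 2 model "with fixed effects for SENSE group status, time, and the interaction between group and time".

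**The concern.** Image acquisition is prescribed for one side of the primary comparison and left open for the other. If automated volumes or FA differ systematically between a 1T and a 3T acquisition, that difference enters the SENSE-versus-reference contrast and cannot be told apart from an exposure effect. It could create an apparent effect or hide a real one. The scanner used at TEA is not a baseline covariate, so the stated adjustment rule does not reach it, and a larger sample would not remove it.

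For Aim 2 no inference about reference scans is needed. SENSE infants move from the in-unit 1T to the off-unit 3T at their last scan, so absolute growth over the final interval is mixed with the change of scanner.

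**Working it through.** **1. The plan's own figure.** Inputs from section 2.8 and the group sizes in section 2.2: 50 SENSE and 25 reference infants, d = 0.70, two-sided alpha 0.05. The noncentrality is d × √(50 × 25 / 75) = 0.70 × 4.082 = 2.858 on 73 degrees of freedom. Power is 80.5% by the noncentral t (81.5% by the normal approximation). The stated figure of at least 80% reproduces. The problem is possible bias, not sample-size arithmetic.

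**2. Effect of a scanner offset.** The documents give neither the 1T–3T difference nor the share of reference scans at 1T, so both are assumed. With all SENSE scans at 3T, the shift in the group contrast is (share of reference scans at 1T) × (offset in SD). For example, half at 1T and an offset of 0.5 SD give 0.5 × 0.5 = 0.25 SD, noncentrality 0.25 × 4.082 = 1.02. The calculation ignores correlation within multiple births and the extra variance from mixing scanners.

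Rejection rate with no true effect (nominal 5%):

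| Offset (SD) | All reference scans 1T | Half 1T |
|---|---|---|
| 0.1 | 6.9% | 5.5% |
| 0.2 | 12.7% | 6.9% |
| 0.3 | 22.7% | 9.3% |
| 0.5 | 52.2% | 17.2% |

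If the offset opposes a true d = 0.70 and all reference scans are 1T, power falls from 80.5% to 67.6%, 52.2%, 36.4% and 12.7% for the same four offsets.

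**3. What a scanner term can do.** There are at most three cells at TEA: SENSE at 3T, reference at 3T, reference at 1T. With exposure and scanner both in the model, the exposure effect is estimated only from SENSE at 3T versus reference at 3T. If the second cell is empty, only the exposure and scanner effects combined can be estimated. Power for that contrast at d = 0.70, with m reference infants scanned at 3T:

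| m | Power |
|---|---|
| 25 | 80.5% |
| 19 | 72.6% |
| 12 | 57.3% |
| 6 | 35.6% |

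**4. Could each SENSE infant's last 1T scan stand in?** It may precede the TEA scan by about 2 weeks. The Introduction says brain volume quadruples over the hospital stay. Assuming linear growth over 12 to 16 weeks, three quarters of the final volume is gained in that time, so 2 weeks is 0.75 × 2/16 = 9.4% to 0.75 × 2/12 = 12.5% of final volume. SENSE infants would then be scanned systematically younger than reference infants, which could introduce a bias as large as the one being removed unless postmenstrual ages (PMA) overlap.

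**The case against.** The strongest reply is that no sentence says reference scans are 1T. The remark about in-unit scanning concerns infants in general, and reference scans may come from other research, so some may be 3T. This stands. A reader might infer that scanner and exposure are completely confounded; the documents support only possible confounding, partial or whole.

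A reader might also take 13% to 52% as the expected false-positive rate. That range requires every reference scan to be 1T and an offset of 0.2 to 0.5 SD, neither of which the documents give. A negligible offset is not excluded, and the direction is unknown.

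On Aim 2, a reader might conclude that the group-by-time analysis is invalid. Both SENSE groups change scanner at the same point, so that contrast is largely protected. Only absolute growth in the last interval is affected.

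It can also be said that a scanner term or harmonisation step belongs in a full protocol or SAP not shown here, and that the study calls itself exploratory. The first is fair for model detail, and the missing term is not in itself the point. But the difference in acquisition is fixed in this document, and step 3 shows that a model cannot repair it if no reference infant has a 3T scan. Exploratory status does not remove a measurement difference tied to exposure, and section 2.8 still claims power for this comparison.

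**Conclusion.** The point holds in a limited form. The TEA scanner is fixed for SENSE infants and uncontrolled for reference infants, so scanner may be partly or wholly confounded with exposure in the primary volume and FA comparisons, and the stated baseline adjustment does not address it. That follows from the text. That many reference scans are 1T is a reasonable inference from sections 2.6 and 2.6.1, not a stated fact.

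The size of any bias cannot be derived from the documents. The illustrative rejection rates (about 13% to 52% if all reference scans are 1T, about 7% to 17% if half are) rest on an assumed offset of 0.2 to 0.5 SD. In Aim 2 the affected quantity is absolute growth over the final interval. The stated power is arithmetically right, but it applies to a same-scanner comparison only if all 25 reference infants have a 3T scan.

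**What to change.** - Record scanner and sequence for every scan, in all groups.
- Make the primary TEA comparison, and all FA comparisons, within scanner and sequence where reference infants have 3T scans. Adjust for PMA at scan and report how many reference infants contribute.
- If few or none have a 3T scan, state that exposure and scanner cannot be separated, and label the pooled comparison accordingly.
- Compare the SENSE infants' last 1T scan with reference 1T scans only as a sensitivity analysis restricted to overlapping PMA.
- For Aim 2, estimate the growth trajectory on the 1T scans. Report the model that includes the 3T TEA scan separately, stating that its last interval contains a scanner change.
- Qualify the power statement in section 2.8 for the same-scanner comparison.

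This needs two recorded variables and changes of wording, with no additional scan. The cost is precision in the primary comparison, as in step 3 of the working, and a main Aim 2 growth model that stops at the last 1T scan.
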